### Intervention strategy of HEP-S—the rationale

Healthy Eating Promotion through Self-regulation (HEP-S) program is grounded on the self-regulation (SR) approach, which has several features that make it unique when it comes to health promotion [19–21]. Grounded on Social Cognitive Theory, SR subsumes the processes that allow individuals to proactively control the personal, behavioral, and environmental influences that impact human behavior, including eating [25]. These processes are intrinsically cyclic and interdependent, open and dynamic, and proceed through three main phases: the preceding phase (forethought), the performance or volitional control phase, and the self-reflection phase [26] [or Planning, Execution, and Evaluation [25, 27]]. The SR process is under the influence of the individual and can, therefore, be taught and improved. Thus, the agent role of the individual throughout the process is key to become in control and autonomous.

Although individuals may be influenced and regulated by external factors and agents, exclusively relying on external regulation does not allow for the individual to develop adaptive competences and skills, such as choosing a healthy snack [20, 28]. Thus, to self-regulate their behavior and become increasingly autonomous, individuals must progressively shift from external regulation to a model that supports and provides feedback. SR can be important in the processes of healthy eating, as individuals who self-regulate their behavior are likely to plan and systematically use a set of cognitive and metacognitive strategies to meet self-set goals [29]. Thus, the effective use of SR strategies to achieve one’s goal is part of a key process in maintaining an individual’s motivation to reach a self-set goal, such as eating healthily [30].

In recent years, SR has started to receive attention as a key predictor of a variety health-related and wellbeing outcomes. For instance, poor SR appears to be a predictor of weight gain, especially in adolescence [18, 20, 31]. Several studies have successfully implemented self-management programs among individuals with various health conditions, such as heart disease [20]. Individuals enrolled in these programs were able to manage their health conditions and improve their quality of life and wellbeing. More recently, research showed that intervention programs designed to improve SR skills are among the most successful to attain healthy eating behaviors and may play an important role for long-term maintenance of this specific behavior [32]. For example, a study showed that a 2-year intervention combining information with SR strategies had a long-term effect on the consumption of fruits and vegetables when compared to the information-only intervention [33].

Nevertheless, evidence in this domain is still scarce. The majority of these programs focus on health promotion within a disease management context, not on prevention and promotion of a long-term healthy lifestyle, and target adults. Thus, the current proposal will address these gaps by focusing on healthy eating promotion, with a preventive emphasis, among elementary school-aged children.

### HEP-S

#### The intervention

HEP-S is a 20-week narrative-based intervention designed to promote healthy eating through the teaching and development of a set of transversal skills and strategies within that domain. Therefore, the intervention will not focus exclusively on conveying knowledge about healthy eating; the goal is rather to stimulate the agent role of children and promote their use of SR strategies and skills. The program will be implemented online using Canvas®. Canvas® is an online learning management system that allows to, among other things, create modules of content, attach files, share materials, create discussion forums, and conduct videoconferences. Each child will be provided with a unique login to the Canvas® of the group.

At the core of this intervention are the narratives. Narratives, or story-tools, are important educational tools that favor child development [34, 35]. They allow readers to reflect on themselves and their behavior through the characters; they instigate the debate and the uncovering of different perspectives on how to cope with everyday dilemmas [25]. Through the characters and plots, these story-tools create opportunities from which the readers can experience and develop autonomous behaviors and promote SR in a given domain (e.g., learning, healthy eating). Extensive extant research has examined and demonstrated the efficacy of using story-tools to promote SR strategies (e.g., [25, 29, 34]). In this study, two narratives will be used as the prompt for, and instigation of, discussion and reflection about healthy eating: specifically, *Yellow’s Trials and Tribulations,* by Rosário, Núñez, and González-Pienda [35], and *The Hill of the Bald Trees and Other Stories* (*O monte das árvores carecas e outras histórias)*, by Rosário, Magalhães, Pérez, and Arias [36].

The program has two main components: (i) the weekly synchronous session and (ii) the weekly parental involvement activity. Table 1 illustrates the anatomy of the intervention; it provides examples of the activities carried on during a typical week of the program, a brief description of that activity, and the rationale behind it.

**Table 1 Tab1:** Anatomy of the online intervention, example of session activities and their rationale

W		Activity	Description	Rationale
**4**	SS	Reading and discussion of Chapter 1 - *YTT*	The chapter introduces the colors of the rainbow (the main characters of the story) and their psychological characteristics (e.g., Violet is strong and courageous).	Introduce the story’s characters and establish a parallel between the characters’ psychological characteristics and reflect how these characters may behave regarding their nutrition.
	PIA	What *color* is my family’s nutrition?	Children will be asked to choose between drawing the rainbow and matching the family members with the colors in terms of their nutrition; or writing about the association between the colors and their family members and their nutrition. In the end, children must take a photo and share it in the forum.	Get to know and become owner of the characters of the story to promote an identification with the plot.
**11**	SS	Reading and discussion of Chapters 9 and 10 – *YTT*	The pic-nic of the problems.	Behavior and emotions analysis; the importance of responsible acting and impulsivity management to solve non-adaptive strategies and behavior barriers and improve adaptive solutions.
	PIA	Barriers to healthy eating	Children will be asked to discuss in family and comment a scenario related to different problems that children face (e.g., lie, fear, tantrum, annoyance), such as “John makes a tantrum in almost every meal because he does not want to eat the soup”. Then, they have to express on the forum their thoughts on why this might happen, what are the consequences of such behavior, and suggest alternative behaviors.	Emotional and behavioral problem characterization, anticipation of consequences, and reflect on adaptive behavior alternatives.

Notes: *W* week, *FTF* face-to-face, *SS* synchronous session, *PIA* parental involvement activity, *YTT* Yellow’s Trials and Tribulations

##### The weekly synchronous session

For each intervention group of children, there will be every week a 60- to 75-min synchronous videoconference session managed by an educational psychologist with the role of facilitator. Each session will take place at each participants’ home, before or after school classes, during an hour selected by the participants. Parents can attend the session if they wish to do so, but cannot participate, and will be invited to partake in the weekly parental involvement task. Each synchronous session will be organized in three stages: (1) summarize last week’s chapter contents (e.g., the colors taught me what a plan is and how to do a plan) and revise previous week’s parental involvement activity, (2) read and explore the narrative in group through the facilitator’s questioning, and (3) reflect and formulate the session’s take-home message. Chapters of the *Yellow’s Trials and Tribulations* [35] and of *The Hill of the Bald Trees and Other Stories* [36] will be used in each synchronous session to prompt children’s metacognitive reflection about their own behavior through the characters’ behaviors. This strategy will allow children to discuss SR strategies in the healthy eating domain. The premise underlying this approach is that after participants discuss and reflect on the subject, they will undergo a change in their beliefs and comprehension of the “what,” “how,” “when,” and “why” of the phenomenon and, consequently, a behavior change [35]. In sum, we aim for children to become the main characters of their own stories, thus adopting an agent role in their health habits.

##### The weekly parental involvement activity

On a weekly basis, children will be prompted to deepen the learning on the SR skills and strategies for healthy eating that was worked through the narrative chapter in the synchronous session. This will be accomplished by instigating participants to complete activities on Canvas® together with their parents and family (e.g., categorize your pantry’s and fridge’s items according to the colors of the traffic light, take a photo, and share it in the forum with your colleague). It is expected that this activity boosts parents’ curiosity, contributes to parents’ involvement in the program, helps parents acquire the knowledge and strategies, and helps parents apply these strategies at home. The content will be released in the platform, and a facilitator (an educational psychologist with training on self-regulated learning (SRL)) will oversee interactions, provide individualized feedback, and promote children’s engagement in the program. Research shows that beliefs about healthy eating have a stronger impact on eating behavior than declarative knowledge about food [17]. The current project will address this concern by focusing on fostering SR skills and strategies about healthy eating. Still, general knowledge about food is necessary in order to know when to apply the SR strategies. Thus, the parental involvement activity will contribute to the promotion of a deep acquisition of declarative knowledge; i.e., factual knowledge will not be delivered directly to the child, it will be sustained by procedural knowledge about the topic [29, 37, 38].

#### The design

This is a 3-arm randomized controlled trial (RCT) with the following: a control group, with no program; an intervention group, with the online narrative-based program; and an enhanced-intervention group, with the online narrative-based program with gamification strategies embedded in the program. Both intervention groups (i.e., the intervention group and the enhanced-intervention group) will have the same narrative-based intervention described in Table 1. The only difference between the two intervention groups is that, in the enhanced online intervention group, gamification strategies will be added to the dynamics of the program. No other intervention components, timings, and materials will differ between these two trial arms. Despite the potential advantages of conducting online interventions, literature on digital interventions to promote behavior change has highlighted that this mode of delivery is associated with high rates of dropout [39]. Thus, one concern among researchers in this field is to devise strategies that mitigate the high rates of dropout and instill engagement in the online intervention [39, 40]. Accordingly, we are implementing the additional gamification strategies in the third group to assess the efficacy of these strategies in promoting engagement with the program and activities.

Gamification consists in the use of game design elements in a non-game context [41]. Non-game contexts can be education [42], health [43], and business [44]. Examples of game design elements are the narrative context, feedback, reputation, ranks, levels, competition, and relational support [41]. Considering the engaging nature of games, it is expected that adding some of their design and motivational features to the non-game contexts [41, 45, 46] will contribute to the (i) creation of engaging and fun contexts or environments, (ii) enhancement of the degree and depth of participants’ engagement, (iii) promotion of learning opportunities, and (iv) motivation of individuals to engage in the task at hand. Table 2 illustrates how gamification was infused in the online program for the enhanced online intervention group.

**Table 2 Tab2:** Gamification elements used in the enhancement-treatment group

Elements*	Objective/rationale**	How it was implemented
Narrative context	Narratives contribute to user engagement. The narrative provides information about the characters and instigates reflection, as well as the establishment of a parallel between the characters’ actions and their own. It guides the behavior and organizes and provides meaning to the activities.	The narrative context within the intervention is created by the activities being conceived as an extension of the narrative/story-tool that children read during the program.
Feedback	Feedback contributes to user engagement. Feedback allows the user to know how things are going and provides hints on what the user needs to address in order to reach their self-set goals.	The educational psychologist provides personalized feedback to each interaction that children engage in their online group. Examples of feedback include: comments, instigation to reflect about some aspect of their behavior, praise of good choices, discourage not so good choices.
Reputations, ranks, and levels	Reputations, ranks, and levels contribute to user engagement. These elements show the users their place in the hierarchy of the group, promoting competition. It also informs other users about particular competencies or talents and sustained achievements that a user might have.	Children can earn points for performing each activity suggested in the platform. Every week there will be a ranking with the children that acquired points that week and the corresponding badge, as well as with information regarding the cumulative rank of the class. By accumulating points, children will progress and become closer to the end-goal.
Competition under rules that are explicit and enforced	Rules contribute to a sense of fairness among users. Rules allow competition to work when they are evenly and impersonally applied.	The rules are made explicit to children in the first session and available in the platform. The educational psychologist will oversee compliance with the rules and is the sole responsible for attributing points and badges, and making the ranking.
Teams	Teams contribute to user engagement. Teams allow interaction opportunities between members, who reveal their personalities and disclose personal experiences while collaborating to reach team goals.	Children are organized into small groups composed by classmates. Children earn points not only for performing the activities but also if their team members perform all the activities. By collaborating to reach team goals, each child will benefit with extra points in the cumulative rank
Time pressure	Time pressure contributes to users’ competition. Time pressure is one key element to create the sense of “uncertain winning conditions”.	At the end of each week the ranking will be made available with the results of each child’s activity for that week. Children will not be able to go back and complete activities that have already expired.

* These descriptors were retrieved from Deterding and colleagues [41]

** The description of the descriptors was based on Byron Reeves and J. Leighton Read article summarizing the “Ten Ingredients of Great Games”. http://www.cedma-europe.org/newsletter%20articles/misc/Ten%20Ingredients%20of%20Great%20Games%20(Apr%2010).pdf

### Goals and expected outcomes

The main purpose of this study is to evaluate the efficacy of an online intervention, narrative-based with or without gamification strategies, designed to promote healthy eating by fostering the use of SR strategies among elementary school-aged children. Thus, the major goals are to promote children’s use of SR strategies for healthy eating, to strengthen their sense of self-efficacy regarding healthy eating, and to increase the consumption of healthy foods. Other goals of the study include the following: increase knowledge about healthy eating and consequences of unhealthy nutrition or lifestyle; contribute to healthier food preferences; and contribute to more positive attitudes and perceptions about healthy eating. Thus, we want to assess the feasibility of conducting an online intervention with this population and examine the advantages of embedding the program with gamification strategies, by comparing it to the program without these strategies.

Overall, it is expected that children taking part of the intervention will, at the end of the intervention, increase their use of SR strategies for healthy eating, enhance their sense of self-efficacy for healthy eating, and increase their consumption of healthy foods. Additionally, it is expected that their knowledge on the topic will increase, that their food preferences become healthier, and that they will display perceptions and attitudes about the topic that are more positive. Lastly, it is expected that participants enrolled in the enhanced-online-intervention group will be more engaged in the intervention than the online-intervention group.

## Methods/design

### Design and procedures

The present protocol design followed the recommended procedures and items to address in a trial protocol, namely SPIRIT (Standard Protocol Items: Recommendations for Interventional Trials) 2013 checklist. As aforementioned, this is an RCT (REGISTRATION NUMBER: NCT04099498) with three groups: a control group, not enrolled in any program; an intervention group, enrolled in the online program; and an enhanced-intervention group, enrolled in the online program with gamification strategies. The sample will be recruited by first contacting public elementary and middle schools from Portugal and inviting them to participate. Orientation sessions will be held at schools for all parents of children in the target grades to explain the project and its rationale and to invite them to enroll their child. The study will be introduced as a program to promote healthy lifestyles among late elementary school-age children, which aims to monitor relevant engagement variables and examine children’s, parents’, and teachers’ perceptions of the utility and feasibility of these interventions.

### Retention and incentives for the participants

The following strategies will be undertaken to minimize attrition. First, prior to the enrollment of children in the intervention, the researchers will organize orientation sessions with parents to present the project and explain its pertinence and rationale. Second, parents who agree to enroll their child in the program will sign a participation agreement form. Third, parents will also be registered into the platform; moreover, reminder e-mails will be sent whenever there is an activity or task available in the platform, as well as the summary of the week’s chapter. Fourth, check-up sessions with parents will be carried mid-through the program. Lastly, to promote completion of follow-up phases, workshops will be offered to participant children, caregivers, and respective teachers about different themes (e.g., homework, inclusion of minorities). Nevertheless, participation is voluntary and, therefore, parents and children will be informed that they can withdraw from the program at any time. For that, participants only have to report their willingness to drop out of the program.

### Informed consent and randomization

During the orientation session, parents who allow their child to participate in the program will complete the first assessment protocol in loco, as well as complete the informed consent form. In the informed consent, the following aspects will be covered: (i) description of the program, accompanied by a timeline, (ii) duties of the parents as guarantors of their child’s involvement in the program, and (iii) what is expected from parents regarding their involvement with the program and its activities. Children will also complete an informed consent form. Additionally, participants will be asked if they agree to the use of their data in case they choose to withdraw from the trial. Participants will be asked for permission for the research team to share relevant data with people from the Universities taking part in the research or from regulatory authorities, where relevant (e.g., the dissemination plan will be presented).

Genuine randomization at the individual level will not be possible as participants originating from the same class and school will have to be allocated to the same treatment condition to prevent between-group contamination. To address this difficulty, each school that accepts to enroll in the study will be randomly attributed a number associated to one of the groups (i.e., control, intervention, and enhanced-intervention) in a 1:1:1 basis. Moreover, for the intervention groups, small groups of five participants each will be randomly created though computed-generated random numbers.

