### Participants

Children from the 5th and 6th grades will be recruited. Children, instead of adolescents, were selected because it is during childhood that the formation of habits and behaviors takes place [47]. Moreover, unlike children, adolescents are on a developmental stage where a sense of autonomy arises, and many adolescents are resistant to interventions [48, 49]. That is, among adolescents, external control (e.g., parents) of food consumption decreases and internal control becomes increasingly predominant in the face of food choices. Moreover, considering the required degree of autonomy and skills on ICT to partake in the study, the late childhood spectrum seemed more feasible to implement the program.

For the purpose of this study, children attending the regular curriculum will be included. We will seek to exclude children attending alternative curricula, i.e., who have been identified by the school office as having special needs, since these children will not have the necessary autonomy required to attend the program. Additionally, despite the preventive nature of the present program, children will not be included/excluded from the intervention based on their weight status, nor will they need an alteration of their usual care pathways (e.g., medication) to participate in the intervention. Specific inclusion criteria include the following:
Access to a computer equipped with a camera and speakers at home;Internet access at home;Parents have to provide a written consent for their children to participate;Children have to provide a written agreement of willingness to participate;Parents have to be willing to participate in parental involvement activities;Parents have to own an e-mail account or be willing to create one.

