### Data monitoring and trial management

The trial will be supervised by a Trial Steering Committee (TSC) directed by the principal investigator (PI) of the trial. The TSC will meet every 4 months to monitor the trial progress, as well as review and manage the data. Besides the PI, the TSC will also include two independent researchers, one educational psychologist and a methodology expert, who are not directly involved in the study, and the CoPI. An independent statistician with no involvement in the trial will conduct all the data analysis and will inform the results to the TSC at a joint meeting. The co-investigators and research assistants of the project will be responsible for all aspects of local organization of the trial (e.g., identify potential recruits, take consent). To ensure the protocol is implemented as planned, the PI will be responsible for managing and supervising the trial and providing direction and administrative support. Three general meetings with the entire group of researchers will be held throughout the project and smaller monthly meetings will be conducted between the PI, the CoPI, and the researchers to monitor the development of activities and ensure compliance with the goals. Lastly, regular meetings will be conducted between the PI, the science manager, and the financial manager of the research center.

This trial does not have a Data Monitoring Committee (DMC) as the current trial is a low-risk intervention, without safety issues or foreseen risks associated. Moreover, the trial does not have a Stakeholder and Public Involvement Group (SPIG) as the researchers that will carry the intervention are trained and certified educational psychologists.

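### The plan does not say whether a school's arm is assigned before or after families consent and complete baseline, and nothing keeps the arm hidden until then

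*Protocol article*

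**What the plan says.** All references are to the protocol article.

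- **Schools come first.** Design and procedures: "The sample will be recruited by first contacting public elementary and middle schools from Portugal and inviting them to participate".
- **Schools are the unit of allocation.** Informed consent and randomization: "each school that accepts to enroll in the study will be randomly attributed a number associated to one of the groups", 1:1:1 across control, intervention and enhanced intervention. The reason given is that "participants originating from the same class and school will have to be allocated to the same treatment condition to prevent between-group contamination".
- **Families are recruited individually.** Design and procedures: "Orientation sessions will be held at schools for all parents of children in the target grades to explain the project and its rationale". At that session, "parents who allow their child to participate in the program will complete the first assessment protocol in loco", and they also sign consent.
- **Consent and eligibility refer to the program.** The consent form covers, among other items, "what is expected from parents regarding their involvement with the program and its activities". An inclusion criterion under Participants reads: "Parents have to be willing to participate in parental involvement activities".
- **Who recruits.** Under Data monitoring and trial management, the co-investigators and research assistants "will be responsible for all aspects of local organization of the trial (e.g., identify potential recruits, take consent").
- **Blinding.** Blinding and data access blinds the external statistician to arm. It also keeps completed assessments from parents and from the psychologist running the sessions. It says nothing about recruiters, schools or parents being unaware of the arm.
- **Timing of baseline.** Table 3 puts consent and anthropometry at registration and the psychological questionnaires at a separate T0 column. It does not place randomisation relative to either.

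**The concern.** In a cluster trial with individual consent, randomising schools protects the comparison only if the families who enrol are not selected with knowledge of the arm. Here one arm applies to a whole school, so anyone who knows one child's arm knows every child's arm in that school.

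A parent who knows the school is in a program arm is deciding about 20 weeks of home sessions and weekly family tasks. A parent who knows it is a control school is deciding about assessments now and the program only later. The families who say yes could differ in motivation, and the article itself treats parental involvement as a driver of adherence and engagement. Recruiters who know the arm could also, without intending to, present the study differently.

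A mixed model with a group-by-time term absorbs stable differences in level. It does not remove a difference in motivation that also affects how fast children change, and a larger sample does not cure that. If T0 self-reports are completed with the arm known, the starting point of the change measure is exposed as well.

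**Working it through.** **1. Order of events.**

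| Step | Stated? | Order relative to allocation |
|---|---|---|
| School invited and accepts | Yes, first | Before (only accepting schools are allocated) |
| Parents' orientation session | Yes, held in the schools | Not stated |
| Parental consent, child agreement, first assessment | Yes | Not stated |
| T0 psychological measures | Yes, Table 3 | Not stated |
| Arm kept from recruiters, schools, parents | Not stated | – |

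The one event attached to allocation is the school's acceptance, which precedes the parents' session. Allocation at acceptance is therefore the natural reading, but it is an inference: no date or sequence is given.

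**2. Which selection would matter.** In the article's three-level model, G is the arm and T is time. The level-3 equations give G a coefficient on the intercept (γ001) and on the slope (γ101). The hypothesis tested is γ101 = 0.

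- If enrolled families differ between arms only in outcome level, the difference goes into γ001 and γ101 is not biased.
- If they differ in change over time, the difference goes into γ101 and cannot be separated from the program effect.

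A calculation of bias would need the correlation between willingness to enrol and change, and consent rates by arm. The article gives neither.

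**3. Direction.** If lower uptake leaves a more motivated group of consenters, lower uptake in control schools biases against the program and lower uptake in program schools biases in its favour. The sign is therefore open.

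**4. What a given bias would do (illustration only).** The article's own figure is a minimum detectable effect of 0.25 at 80% power, with N1 = 5 measures, N2 = 15 children, N3 = 40 classrooms per arm, ρ1 = 0.5 and slope variance 0.1. I assume equally spaced times 0 to 4, so Var(T) = 2, and total variance σ² = 1. The stated figure is recovered when the slope variance is added as N1·Var(T)·0.1:

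- Variance of the slope contrast = 2 × (0.5 + 5 × 2 × 0.1) / (5 × 15 × 40 × 2) = 3/6000 = 0.0005.
- Standard error of the difference at the last time point = 4 × √0.0005 = 0.0894.
- Minimum detectable effect = (1.960 + 0.842) × 0.0894 = 0.251, with power 0.798 at 0.25.

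With no true effect and an assumed bias b in change at the last time point, the two-sided error is 1 − Φ(1.96 − b/0.0894) + Φ(−1.96 − b/0.0894):

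| Assumed b (SD) | Type I error |
|---|---|
| 0 | 5.0% |
| 0.025 | 5.9% |
| 0.05 | 8.6% |
| 0.10 | 20% |

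These values of b are not in the article and do not predict what will happen. A larger true standard error would make the inflation smaller for the same b.

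**The case against.** The strongest reply is that the article never says schools are randomised before families consent. The clause about accepting schools can be read as saying which schools are allocated, not when. The section describes consent and the first assessment before it describes allocation, which is weak evidence for the opposite order. This stands: a reader might infer that randomisation before consent is the stated plan, and the text does not support that. What it supports is that the order is left open and nothing secures the safe one.

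Second, Safety aspects and ethical considerations offers controls the program once all assessments are done. The consent items on parental duties and the willingness criterion can therefore mean something to control families too. This also stands. It narrows the difference between the two decisions, but an immediate program and one offered after the last follow-up are not the same offer, and the arm is still not hidden.

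Third, the article describes one general introduction for all parents in the target grades, one consent content and one set of criteria. A reader might infer arm-specific scripts or forms; nothing in the text suggests them. A common script does not, however, conceal the arm.

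Fourth, an article condenses a fuller protocol. That carries little weight here, because the article has its own sections on randomisation and blinding and says it follows SPIRIT. The order of consent and allocation is also not a detail usually left to an analysis plan.

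**Conclusion.** The point holds in a limited form. The plan ties allocation to accepting schools, recruits families individually inside those schools, does not state the order, and describes no safeguard that keeps the arm from recruiters, schools or parents until consent and T0 are closed. As written, it permits enrolment and baseline reporting with the arm known.

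The size and direction of any resulting bias cannot be derived from the document. It would be tempting to say that a given share of the 0.25 target effect could be spurious. That would need assumed consent rates and an assumed correlation with change, and a correlation with outcome level would not do, because the test is on the slope. The error rates above show only that a bias in change which is small against 0.25 would matter at this precision, under the stated assumptions.

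The change should be made. If the intended sequence already conceals allocation, saying so settles the matter.

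**What to change.** In Informed consent and randomization, state that a school's allocation is generated, or disclosed to anyone involved in recruitment, only after parental consent, child agreement and all T0 measures are complete in that school. The sentence should cover T0 and not only registration, since Table 3 separates the two. Commit to reporting the numbers approached and consenting in each arm, so that differential uptake can be seen.

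The cost is a short delay in telling schools their arm and in scheduling sessions. No extra participants or staff are needed. Trial status says that recruitment had not begun at submission, so the order could still be fixed at that point; if schools have since been allocated, the order actually followed should be reported.
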